| **Study period:** Approximately 90 days | **Phase of development:** Phase 3 |
| **Objectives**  The objectives of this study are to determine the safety, tolerability, and nutrient absorption of enteral nutrition administered through the RELiZORB enzyme cartridge for a total of 90 days. Measurements will be assessed at baseline and on study Day 7, 14, 28, 60, 90 for in-clinic assessments and weekly for at-home assessments in pediatric subjects with short bowel syndrome (SBS), aged 2 years – 18 years, who are dependent on parenteral nutrition (PN).  Primary objective:   - To evaluate the effect of the RELiZORB enzyme cartridge when used with enteral nutrition daily for 90 days on the change from baseline in PN calories.   Secondary objective:   - To evaluate the effect of the RELiZORB enzyme cartridge when used with enteral nutrition daily for 90 days on the change from baseline in body weight (weight-for-age z-score).   Safety objectives:  To evaluate the safety and tolerability of the RELiZORB enzyme cartridge when used with enteral nutrition daily for 90 days, by examining:   - The incidence of grade 2 or higher adverse events. All adverse events will be collected by participants, including diarrhea, changes in stool consistency (Bristol scale)/ amount/frequency (if applicable), increased ostomy output (if applicable, defined as >2.5 mL/kg/hour), the need to decrease enteral feeds, changes in urine color assessed by Dehydration Color scale, and discontinuation from the study treatment. - The incidence of abnormalities in vital signs (blood pressure, pulse rate, respiratory rate, temperature). - The incidence of abnormalities in hematology and biochemistry parameters based on Boston Children’s Hospital reference ranges. Clinical lab evaluations will include sodium, potassium, chloride, CO2, glucose, blood urea nitrogen (BUN), creatinine, calcium, phosphorus, magnesium, alkaline phosphatase, albumin, pre-albumin, total protein, total and direct bilirubin, triglycerides, cholesterol, high-density lipoprotein (HDL), very low-density lipoprotein (VLDL), low-density lipoprotein (LDL), C-reactive protein (CRP), AST, ALT, GGT and fatty acid profile.   Exploratory objectives:   - To evaluate the effect of the RELiZORB enzyme cartridge when used with enteral nutrition daily for 90 days on the change from baseline in nutrient absorption as measured by 72-hour total fecal fat, coefficient of fat absorption, and fecal fatty acid composition. - To evaluate the effect of the RELiZORB enzyme cartridge when used with enteral nutrition daily for 90 days on the change from baseline in plasma fatty acid composition. - To evaluate the effect of the RELiZORB enzyme cartridge when used with enteral nutrition on growth as measured by height and head circumference (in children <36 months of age) using adjusted-for-age Z-score. - To evaluate the effect of the RELiZORB enzyme cartridge when used with enteral nutrition daily for 90 days on the change from baseline in BMI z-score. - To evaluate the effect of the RELiZORB enzyme cartridge when used with enteral nutrition daily for 90 days on the change from baseline in PN volume. - To evaluate the effect of the RELiZORB enzyme cartridge when used with enteral nutrition daily for 90 days on the change from baseline in total enteral calories and total enteral volume. - To evaluate the effect of the RELiZORB enzyme cartridge when used with enteral nutrition daily for 90 days on the change from baseline in total oral calories and total oral volume. - To evaluate the effect of the RELiZORB enzyme cartridge when used with enteral nutrition daily for 90 days on the ability to wean from PN. | |

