## EXPLORATORY OBJECTIVES

- To evaluate the effect of using the RELiZORB enzyme cartridge with enteral nutrition when used daily for a total 90 days of treatment, on the change in fat absorption as measured by 72-hour total fecal fat and fatty acid composition in pediatric subjects with SBS who are PN dependent, aged 2 years – 18 years.
- To evaluate the effect of using the RELiZORB enzyme cartridge with enteral nutrition when used daily for a total 90 days of treatment, on the change in plasma fatty acid composition and fat-soluble vitamins (A, D, E, and K) in pediatric subjects with SBS who are PN dependent, aged 2 years – 18 years.
- To evaluate the effect of using the RELiZORB enzyme cartridge with enteral nutrition when used daily for a total 90 days of treatment on growth in pediatric subjects with SBS who are PN dependent, aged 2 years – 18 years, by measuring height (assessed with height-for-age z-score) and head circumference (assessed with head circumference-for-age z-score in children < 36 months of age).
- To evaluate the effect of using the RELiZORB enzyme cartridge with enteral nutrition when used daily for a total 90 days of treatment on BMI z-score in pediatric subjects with SBS who are PN dependent, aged 2 years – 18 years.
- To evaluate the effect of using the RELiZORB enzyme cartridge with enteral nutrition when used daily for a total 90 days of treatment on PN dependency in pediatric subjects with SBS who are PN dependent, aged 2 years – 18 years, by recording PN volume.
- To evaluate the effect of using the RELiZORB enzyme cartridge with enteral nutrition when used daily for a total of 90 days of treatment on enteral nutrition tolerance in pediatric subjects with SBS who are PN dependent, aged 2 years – 18 years, by recording total enteral calories and volume.
- To evaluate the effect of using the RELiZORB enzyme cartridge with enteral nutrition when used daily for a total of 90 days of treatment on oral nutrition tolerance in pediatric subjects with SBS who are PN dependent, aged 2 years – 18 years, by recording total oral calories and volume.
- To evaluate the effect of using the RELiZORB enzyme cartridge with enteral nutrition when used daily for a total of 90 days of treatment on the ability to wean from PN at any time during the course of the study.

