### Standard of Care

All subjects will receive standard medical, surgical, and nutritional care during the study. Standard nutritional care will be provided as follows:

- All subjects without existing central venous catheters will undergo placement of these catheters for intravenous fluid management and administration of hypertonic nutrition solutions.
- PN will be increased when oral energy intake declines to less than baseline resting energy requirements for more than 3 days or the patient’s underlying clinical condition is such that PN should be initiated immediately so as to maintain protein stores.
- Maintenance fluid requirements for all subjects will be calculated according to the Holliday-Segar Method, detailed in Table 3.
- Amino acids will be provided according to standard, age-adjusted estimations for subjects receiving parenteral nutrition, detailed in Table 4.
- The nutritional regiment for subjects is provided in Table 5.

Table 3. Daily Fluid Requirements by Body Weight, According to the Holliday-Segar Method

| **Daily Fluid Requirements** | |
| --- | --- |
| **Body weight** | **Maintenance Parenteral Fluid Requirements** |
| 0 to 10kg | 100 mL / kg |
| 10 - 20 kg | 1000 mL + 50 mL / kg over 10 |
| Over 20 kg | 1500 mL + 20 mL / kg over 20 |

Table 4. Daily Caloric and Protein Requirements

| **Daily Caloric and Protein Requirements** | | |
| --- | --- | --- |
| **Age** | **kcal/kg/day** | **Protein g/kg/day** |
| 1 to 7 years | 75 to 90 | 1.5 to 3 |
| 7 to 10 years | 50 to 75 | 1.5 to 3 |
| 11 to 12 years | 50 to 75 | 0.8 to 2.5 |
| 13 to 18 years | 30 to 50 | 0.8 to 2.5 |

Table 5. Nutritional Regimen

| Dietary Component | Dose |
| --- | --- |
| Fat (enteral) | No more than 40% of total calories (PN + EN) |
| Electrolytes | As per clinical needs |
| Vitamins | >3 kg and <11 years of age: 5 ml/day MVI Pediatric^®^  >11 years of age: 1 vial MVI 13 (contains 150ug vitamin K) |
| Trace elements | As per clinical needs |

[**7.1.6**](#_MEASUREMENTS_AND_EVALUATIONS)  **Analysis of fecal fat and fatty acids profiles**

Prior to receiving the study device, a 72-hour stool collection will be obtained during the enrollment period for fecal fat and fatty acid analysis. This process will be repeated prior to the final study visits. Throughout the study, plasma samples will also be collected for fatty acid analysis.

*Protocol:*

1. Collected stool is homogenized, weighed and a representative sample is taken.

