2. *Quantitative total fat*: The collected stool sample is sent to BCH central lab for quantitative total fecal fat measurement
   1. The coefficient of fat absorption will be calculated using the total stool mass, total fat analysis, and the following equation:

CFA= [Total Dietary fat (72 hours) – Total Stool Fat (72 hours)] ÷ Total Dietary Fat (72 hours)

1. *Stool and Plasma Fatty acid profile* :

Stool and plasma fatty acid composition will be analyzed at OmegaQuant Analytics by gas chromatography (GC) with flame ionization detection. Stool samples will be weighed into a screw-cap glass vial which contain tritricosanoin as an internal standard (tri-C23:0 TG) (NuCheck Prep, Elysian, MN), homogenized and then extracted with a modified Folch extraction. A portion of the organic layer will be transferred to a screw-cap glass vial and dried in a speed vac. After samples are dried BTM (methanol containing 14% boron trifluoride, toluene, methanol; 35:30:35 v/v/v) (Sigma-Aldrich, St. Louis, MO) is added. The vial is briefly vortexed and heated in a hot bath at 100˚C for 45 minutes. After cooling, hexane (EMD Chemicals, USA) and HPLC grade water is added, the tubes are recapped, vortexed and centrifuged help to separate layers. An aliquot of the hexane layer will be transferred to a GC vial. GC will be carried out using a GC-2010 Gas Chromatograph (Shimadzu Corporation, Columbia, MD) equipped with a SP-2560, 100-m fused silica capillary column (0.25 mm internal diameter, 0.2 um film thickness; Supelco, Bellefonte, PA).

1. Fatty acids are identified by comparison with a standard mixture of fatty acids (GLC OQ-A, NuCheck Prep, Elysian, MN) which was also used to determine individual fatty acid calibration curves. Fatty acid composition is expressed as a percent of total identified fatty acids and concentrations as µg/mg of stool.

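### The exploratory stool fatty-acid results are expressed only in relative units and per mg of stool, neither of which gives the amount of a fatty acid excreted (Protocol Section 7.1.6; minor)

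*Protocol*

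**What the plan says.** The Synopsis (Exploratory objectives) speaks of "nutrient absorption as measured by 72-hour total fecal fat, coefficient of fat absorption, and fecal fatty acid composition". Section 2.4 speaks of "change in fat absorption as measured by 72-hour total fecal fat and fatty acid composition". In both places the fatty acid profile stands as a measure of absorption. The lists of outcomes differ: the Synopsis (Criteria for evaluation) pairs 72-hour fecal fat with the CFA, while Section 3.3.4 pairs fecal fat composition with the CFA.

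Section 7.1.6 describes the laboratory work. Its first step reads "Collected stool is homogenized, weighed and a representative sample is taken". For total fat, "The collected stool sample is sent to BCH central lab for quantitative total fecal fat measurement". Then: "The coefficient of fat absorption will be calculated using the total stool mass, total fat analysis, and the following equation", which takes dietary fat less stool fat, divided by dietary fat, over the 72 hours. For the individual fatty acids the section ends with the units: "Fatty acid composition is expressed as a percent of total identified fatty acids and concentrations", the concentrations being in µg per mg of stool. It gives no amount per 72 hours and no absorption coefficient for any single fatty acid.

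**The concern.** A measure of absorption from stool has to start from how much was excreted. The two stated units do not supply this.

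- **Percent of the profile** is relative. If every fatty acid is absorbed better to the same degree, the profile looks the same as at baseline.
- **µg per mg of stool** has stool mass in its denominator. Section 7.1.6 weighs stool into the vial before extraction, and the only drying it describes is of the extracted layer afterwards. As written, the concentration is therefore per mass of undried stool and depends on its water content. Stool consistency, stool amount and ostomy output are followed as possible effects of treatment (Sections 2.3 and 3.3.3), so the denominator may itself change between the two collections.

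At stake is the reading of the individual stool fatty acids. The protocol presents the device as helping with long-chain fatty acids such as DHA, EPA and ARA (Synopsis, Test product; Section 1.1), and the stool profile is the only planned fecal measure that separates them.

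**Working it through.** The protocol gives no expected value, standard deviation or power for the fecal measures, so there is no figure of its own to reproduce. The check is a mass balance.

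**Inputs from the protocol:** the two units, the weighing of the whole collection and the form of the CFA (all Section 7.1.6).

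**Assumed inputs, for illustration only:** dietary fat 90 g per 72 h; stool fat at baseline 36 g, made up of 18 g linoleic, 12 g oleic and 6 g saturated fatty acids; stool mass 600 g. The fatty acids are taken to sum to total stool fat.

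**Formulas**
- Percent = one fatty acid ÷ sum of fatty acids
- Concentration in µg/mg (the same number as mg/g) = 1000 × grams of the fatty acid ÷ grams of stool
- Amount in g/72 h = concentration × stool mass in g ÷ 1000
- CFA = (dietary fat − stool fat) ÷ dietary fat

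**Results for linoleic acid**

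| Case | Excreted, g | Stool mass, g | Percent | µg/mg | µg/mg × mass, g | CFA |
|---|---|---|---|---|---|---|
| A. Baseline | 18 | 600 | 18/36 = 50% | 30 | 18 | (90−36)/90 = 60% |
| B. Same excretion, wetter stool | 18 | 1200 | 18/36 = 50% | 15 | 18 | 60% |
| C. Half the excretion, same mass | 9 | 600 | 9/18 = 50% | 15 | 9 | (90−18)/90 = 80% |
| D. Half the excretion, half the mass | 9 | 300 | 9/18 = 50% | 30 | 9 | 80% |

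The percentage is 50% in all four cases. The concentration cannot tell B from C, although excretion is unchanged in B and halved in C. It also cannot tell A from D. Concentration times mass returns the excreted amount every time, and the planned CFA separates the cases for total fat.

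The concentration can also move the wrong way. Take 3 g of a fatty acid, first in 1500 g and then in 1000 g of stool (again assumed values). The concentration goes from 2 to 3 µg/mg, a ratio of 1.50, while excretion is unchanged, a ratio of 1.00.

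**Can the CFA stand in for the individual fatty acids?** Section 1.2, Table 1 gives DHA plus EPA for three formulas: 1.2 of 27 g fat (4.4%), 1.9 of 26 g (7.3%) and 2.45 of 32 g (7.7%). Suppose such a formula were the only dietary fat, and absorption of DHA plus EPA alone rose by 50 percentage points. The CFA would then move by 0.5 × 4.4 to 0.5 × 7.7, that is 2.2 to 3.8 points. So the CFA answers the question for total fat but says little about these fatty acids.

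**The case against.** **The absorption objective does not rest on the profile.** A reader might infer from Section 7.1.6 that fat absorption as a whole will be judged from stool water and relative mix. The protocol does not support that. The same section plans quantitative total fecal fat and a CFA that uses total stool mass and is scaled to intake, and the Synopsis names both in the objective. This stands in full and confines the point to the fatty-acid component.

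**DHA and EPA are followed in plasma.** Plasma fatty acids are measured at Days 7, 14, 28, 60 and 90 (Section 3.3.4), and the earlier device studies described in Section 1.2 rest on plasma. This stands, and it lowers the weight of the stool profile. It does not make the stool units a measure of absorption, which is how the objectives list the profile.

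**The sentence may only report assay units.** It closes a description of gas chromatography, and a derived amount could be defined in a statistical analysis plan. That is a fair reading, and such a definition would settle the matter. Still, the protocol itself names composition as an absorption measure and itself fixes the units, without saying that the multiplication will be done.

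**The effect should not be overstated.** A reader might infer that the profile could show no change while absorption doubles. Halving excretion doubles absorption only if 1 − E/2 = 2(1 − E), where E is the fraction excreted. That gives E = 2/3, a baseline absorption of one third. From the 60% assumed above, absorption rises to 80%, which is 1.33-fold.

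**Conclusion.** The point holds for the exploratory stool fatty-acid component only, and it is minor. Neither percent composition nor µg/mg of undried stool gives the amount of a fatty acid excreted, although the Synopsis and Section 2.4 list composition as a measure of absorption. That follows from the definitions of the units. The gram figures above are assumed and show only the mechanism, and the dependence on water rests on stool being weighed undried, as Section 7.1.6 describes. How far stool mass will change between the two collections cannot be judged from the protocol. Total fecal fat and the CFA over 72 hours are not affected, nor are the primary, secondary and safety endpoints.

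**What to change.** In Section 7.1.6, state that each stool fatty acid concentration is multiplied by the total 72-hour stool mass weighed in the first step, and that the result is analysed as g/72 h. Say that percent composition and µg/mg are kept as descriptive results and are not read as absorption. This costs one sentence and one multiplication, because both factors are already collected.

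An amount in g/72 h measures excretion and is still not scaled to intake, and enteral feeding may be advanced between the two collections. Where the fatty acid content of formula and food is known, a coefficient for the individual fatty acid, in the form of the CFA equation, may be added. This part is optional and not free: Sections 6.1 and 7.1.1 record intake as fat, carbohydrate and protein, so fatty acid contents would have to be looked up and may not always be available.

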# DATA AND SAFETY MONITORING BOARD (DSMB)

The Data Safety Monitoring Board (DSMB) will be an independent board comprised of three physicians and a biostatistician not participating in this study. Considering this being an open label study committee, membership will include three independent clinicians who are expert in the field, and one biostatistician. One of the clinicians will be appointed as chairman of the DSMB. The DSMB is responsible for safeguarding the interests of study participants, assessing the safety and efficacy of study procedures, and for monitoring the overall conduct of the study. Specific details about the DSMB composition, responsibilities, organization and meeting frequency can be found in the DSMB Charter.

# PROCEDURES FOR HANDLING ADVERSE EVENTS AND SERIOUS ADVERSE EVENTS

## DEFINITION OF AN ADVERSE EVENT

The following definition of adverse event (AE) will be used for this study:

- Adverse event means any untoward medical occurrence associated with the use of a device in humans, whether or not considered device-related.
- All AE’s post-baseline will be captured. Adverse events grade 2 or higher will be analyzed.

An adverse event can be any unfavorable and unintended sign (including an abnormal laboratory finding), symptom, or disease (new or exacerbated) temporally associated with the use of the investigational product, regardless of whether it is considered to be related to the investigational product.

Examples of AEs include the following:

- Significant or unexpected worsening or exacerbation of the indication under study
- Exacerbation of a chronic or intermittent preexisting condition including an increase in frequency or intensity of the condition
- New conditions detected or diagnosed after investigational product administration even if they were present before the start of the study
- Signs, symptoms, or the clinical sequelae of a suspected interaction with another medical product
- Signs, symptoms or the clinical sequelae of a suspected overdose of either investigational product or a concurrent medication

Overdose will not be reported as an AE or serious adverse event (SAE), but rather the symptoms resulting from the overdose.

Examples of AEs do not include the following:

- Situations that are unwanted by the subject but in which an untoward medical occurrence did not occur, for example social inconvenience after admission to a hospital
- Anticipated day-to-day fluctuations of a preexisting disease or condition (present or detected before enrollment) that does not worsen overall
- Expected progression of the disease being studied, including signs or symptoms of the disease, unless progression is more severe than expected for the subject’s condition
- The Common Terminology Criteria for Adverse Events (CTCAE) version 5 (https://ctep.cancer.gov/protocoldevelopment/electronic_applications/docs/CTCAE_v5_Quick_Reference_5x7.pdf) will be used to grade toxicities.

The investigator is responsible for performing periodic and special assessments for AEs. The investigator and study personnel will note all AEs mentioned by the subject after administration of the investigational product. Any significant clinical finding detected prior to administration of the study device will be included in the subject’s medical history. All clinical complaints volunteered by or elicited from the subject during the study will be recorded on the appropriate page of the CRF for the study period indicated. The subject will receive appropriate treatment and medical supervision for any AE that occurs. Subjects with anaphylactic or allergic reactions will not continue to receive the study device.

All AEs judged to be clinically significant, including clinically significant laboratory abnormalities, will be followed until resolution. All AEs will be summarized in the annual report or more frequently if requested by the regulatory agency. SAEs require special reporting in addition to documentation in the CRF as described in Section 9.8.

## DEFINITION OF A SERIOUS ADVERSE EVENT

In this clinical trial, a serious adverse event is defined as an AE that meets any of the following criteria:

- Results in death
- Is life-threatening

The term life-threatening in the definition of an SAE refers to an event in which the subject was at risk of death at the time of the event. Life‑threatening does not refer to an event that hypothetically might have caused death if it were more severe.

- Requires hospitalization or a prolongation of an existing hospitalization

In general, hospitalization signifies that the subject has been detained at the hospital or emergency ward for observation or treatment that would not have been appropriate in the physician’s office or out-patient setting. Complications that occur during hospitalization are AEs, but not necessarily SAEs. An occurrence or complication that prolongs hospitalization is an SAE. When there is doubt as to whether hospitalization occurred or was necessary, the AE will be considered an SAE. Hospitalization for elective treatments of a preexisting condition that did not worsen from its original baseline level is not considered an SAE.

- A persistent or significant incapacity or substantial disruption of the ability to conduct normal life functions

This definition is not intended to include AEs of relatively minor medical significance such as uncomplicated headache, nausea, vomiting, diarrhea that may interfere or prevent everyday life functions but do not constitute a substantial disruption.

- Other important medical event

Medical or scientific judgment will be exercised in deciding whether reporting is appropriate for other important medical events that may not result in death, be life-threatening, or require hospitalization but still may jeopardize the subject or may require medical intervention to prevent one of the outcomes listed in this definition. These events will also be considered serious. Examples of such events are intensive treatment in an emergency room or at home for allergic bronchospasm, blood dyscrasias or convulsions that do not result in hospitalization, or development of drug dependency or drug abuse.

An SAE requires additional detailed reports and follow-up. The content of these detailed reports must address the investigator’s estimate of causality. The principal investigator will review the SAE to determine if it is an expected SAE (i.e., whether or not the SAE is identified in nature, severity, and frequency in the Investigator’s Brochure).

